#### 2.3.2. Exclusion Criteria

The data of those patients who have had to apply another therapy (pharmacological, surgical, or rehabilitative) during the care provided by the physiotherapist in their usual clinical practice will not be included. For ethical reasons, this will not be explicitly explained to the families who agree to participate in this study, so as not to influence possible therapeutic decisions in the following two months. Data of the children will be followed up and can be excluded later if there is a change in their diagnosis and cerebral palsy is not confirmed at the appropriate age. The previous therapeutic trajectory, as well as concomitant treatment (such as pharmacological treatment for spasticity, dystonia, epilepsy, etc., as well as other rehabilitation interventions) was not considered within the exclusion criteria for two reasons: their effect would already be included within the rate of motor development before VT, and also because all the children were compared only to themselves. These will be noted and considered during the calculations, but the data exclusion will only occur if there are changes in them (both adding or withdrawal) during our 2 months of intervention. 

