## 2. Materials and Methods

### 2.1. Study Design

A pseudo-randomized clinical trial has been designed that will assess gross motor function before the physiotherapy intervention (with Vojta therapy or conventional physiotherapy intervention, such as environmental enrichment and task-specific training) and two months after its application. The clinical trial has been conducted according to the consolidated standards of reporting trials (CONSORT) statement [40]. The current treatment protocol is described according to the recommendations of SPIRIT [41].

Patients are assigned to one treatment or another following criteria of immediacy as part of the regular routine of the rehabilitation service. Therefore, the randomization of the sample is possible following the natural ordering of the rehabilitation service where the study is carried out. The participants in this research, within their care routine and according to the health protocols established in the service, will be assigned to one of the two study groups:Intervention group: patients under Vojta Therapy intervention [17,18,19,20,21,22,23,24,25,26,27,28]Control group: patients under regular physiotherapy intervention, such as environmental enrichment and task-specific training [25]

This methodology will be useful to provide a service evaluation of the operation of the rehabilitation service itself.

Neither the therapists nor the evaluators of the GMFM may be blinded to the type of treatment administered due to the organization of the rehabilitation service where the study is carried out, as well as the “face-to-face” requirements for carrying out the Vojta therapy and the evaluation of that scale. However, the assessment of the Infant Motor Profile (IMP) is performed by observing a protocolized video recording. This allows the quantification of this factor by an evaluator external to the service (in this case the external principal investigator). This will not only allow us to blind the evaluator regarding the type of intervention that the child receives, but also whether the video belongs to pre- or post-intervention groups. To do this, the videos will be sent after being encrypted and randomized for quantification. 

The study was approved by the Research Ethics Committee of the University of Murcia (1823/2018) and Comité de Ética de la Investigación de A Coruña-Ferrol (2022/099). This trial has been registered under the following code: ClinicalTrials.gov Identifier: NCT0609261.

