#### 2.3.1. Inclusion Criteria

Male and female children between 0 and 36 months, with a risk of neurological alteration or diagnosis of cerebral palsy or neuromotor disease, who are admitted for assessment and/or treatment according to the Vojta therapy methodology or conventional treatment in the Physical and Rehabilitation Medicine Service will be included in this study. The diagnosis may be clinical and/or supported by the presence of lesions in complementary tests. Due to the fact that the diagnosis of cerebral palsy is confirmed in many cases after one year of life, the data of children in treatment for risk of neurological alteration will only be included retrospectively when said diagnosis has been confirmed. Younger children have not received a definite diagnosis of CP yet, but, based on the presence of lesions determined by magnetic resonance imaging, their risk of developing CP was estimated to be sufficiently high to justify their inclusion in the CP group. 

Parents or guardians must sign the informed consent that will allow us to use their data on therapeutic results, always in a pseudonymized (coded) way, guaranteeing confidentiality. 

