## 3. Methods and Timeline

Phase 1. Initial Assessment: Children who go to the rehabilitation center where they have been referred will be treated, an initial routine clinical examination will be performed, including: Personal/medical data collection.GMFM quantification.Treatment with the physiotherapist.Training of the parents in the home program.Recording for the IMP quantification.

Phase 2. Intervention period (2 months): The assignment to the therapist will be randomized according to the needs of the service, where each therapist will adapt the treatment according to the initial assessment. Both assessors and therapist cannot be blinded to the allocation or treatment, and both required live-direct performance. An external assessor (blind to both) will be able to score the IMP recordings. 

Children will receive weekly or fortnightly treatment, and their parents, family members, or carer will be trained in carrying out a home program. Each therapist will adapt the treatment according to the initial evaluation, as is usually performed in the rehabilitation service. During the treatment sessions, the physiotherapist will apply the therapy directly, either based on Vojta therapy or conventional physiotherapy. The frequency of repetition of the treatment at home and in the hospital will be recorded, depending on the availability of each family and the normal functioning of the service.

Phase 3. Second assessment at 2 months (±1 week, depending on follow up appointments).

Collection of data on the possible changes made in previous treatments and the frequency of home treatment (possible incidents due to illness or family limitations).GMFM quantification.Recording necessary for IMP quantification.

Children carried on clinically with the intervention, but this short period would allow us to attribute changes to RL, controlling better the influence of other factor (such as age maturation or other therapy inputs).

Study length. The data collection will be carried out for 4 years from the approval of the CEI. Only patients receiving healthcare with any of the therapies under investigation after authorization by the CEI will be included.

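### Children can be removed from, or admitted to, the analysis after treatment according to later CP confirmation and therapy changes, which leaves the group comparison open to outcome-related selection bias

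*Protocol article*

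**What the plan says.** Two rules in the protocol article decide, after assignment, whose data count.

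- **Diagnosis rule.** Section 2.3.2 says that a child's data "can be excluded later if there is a change in their diagnosis and cerebral palsy is not confirmed at the appropriate age". Section 2.3.1 has a counterpart: data of children treated for risk of neurological alteration "will only be included retrospectively when said diagnosis has been confirmed". The next sentence of 2.3.1 takes in younger children without a definite diagnosis because, on MRI lesions, "their risk of developing CP was estimated to be sufficiently high to justify their inclusion in the CP group". On how the diagnosis is made: "The diagnosis may be clinical and/or supported by the presence of lesions in complementary tests".
- **Therapy-change rule.** Section 2.3.2 leaves out "patients who have had to apply another therapy (pharmacological, surgical, or rehabilitative) during the care provided by the physiotherapist". It then explains that concomitant treatment as such is tolerated and that "the data exclusion will only occur if there are changes in them (both adding or withdrawal) during our 2 months of intervention".

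Section 3 places the "Collection of data on the possible changes made in previous treatments and the frequency of home treatment" at the two-month assessment, alongside GMFM scoring and the IMP recording. Section 2.1 states: "Neither the therapists nor the evaluators of the GMFM may be blinded to the type of treatment administered". The Statistical Methods section sets out a repeated-measures ANOVA with treatment group as the between-subject factor.

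**The concern.** A comparison of two groups is protected only if membership of the analysed set does not depend on what happened after assignment. Here it can, by two routes.

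First, a CP diagnosis may be purely clinical, and section 2.3.1 notes that it is often confirmed only after the first birthday, so in many children after the two-month outcome. A clinical diagnosis rests partly on motor function, which GMFM and IMP measure. A child who does well is more likely to be one in whom CP is not confirmed. If Vojta therapy works, such children would be more numerous in the Vojta arm.

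Second, adding or withdrawing another treatment can follow poor or good progress; section 2.3.2 itself speaks of patients who had to have the other therapy. Staff who know the arm may make such changes at different rates in the two groups.

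Nothing limits removal to facts fixed before assignment or requires confirmation to be judged blind to arm. The permissive wording of the diagnosis rule adds discretion. Section 2.3.2 defends its tolerance of other treatments by saying that each child serves as his or her own comparator, but that cannot protect an analysis in which group is a factor.

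**Working it through.** **Plan's own figure.** There is none to reproduce on this point. Section 2.6 gives 30 per group, with no effect size, SD, power or allowance for removals. Everything below rests on assumed values and shows what the rules could do, not what they will do.

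**Model (assumed).** Outcome Y has SD 1, mean 0 in controls and δ in the Vojta arm. A latent tendency L has correlation ρ with Y within each arm, variance 1, and mean 0 (control) or ρδ (Vojta).

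**1. Diagnosis rule, same cut-off in both arms.** A child is removed if L > c, with c chosen so that 20% of controls go: c = 0.8416.

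- Control mean after removal: −ρ·φ(c)/Φ(c) = −ρ × 0.2800/0.80 = −0.350ρ.
- Vojta mean after removal: δ − ρ·φ(a)/Φ(a), with a = c − ρδ.

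With δ = 0.5:

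| ρ | a | φ(a)/Φ(a) | Vojta mean | Control mean | Difference | Vojta removed |
|---|---|---|---|---|---|---|
| 1.0 | 0.3416 | 0.3763/0.6337 | −0.094 | −0.350 | 0.26 | 37% |
| 0.7 | 0.4916 | 0.3535/0.6885 | 0.141 | −0.245 | 0.39 | 31% |
| 0.3 | 0.6916 | 0.3141/0.7554 | 0.375 | −0.105 | 0.48 | 24% |

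At ρ = 1, cut-offs of 10% and 30% give 0.32 and 0.21 SD; at ρ = 0.7 they give 0.42 and 0.36 SD. With δ = 0, a = c in both arms and the difference is exactly 0: a common rule with no treatment effect produces no bias.

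**2. Therapy-change rule, poor progressors removed from one arm only, δ = 0.** Removing the lowest fraction q of L shifts that arm's mean by ρ·φ(z_q)/(1 − q). For q = 15%, 0.2332/0.85 = 0.274, so the spurious difference is 0.27 SD (ρ = 1), 0.19 SD (ρ = 0.7) or 0.08 SD (ρ = 0.3).

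**3. Consequence for the test at 30 per group** (ρ = 0.7, two-sided 5%, normal approximation, simulated means and SDs).

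- No true effect, worst 20% removed from one arm only: shift 0.246, SD 0.947, 24 against 30 children. SE = 0.947 × √(1/24 + 1/30) = 0.259, and the false-positive rate is about 16%.
- No true effect, worst 20% removed from one arm and 10% from the other: shift 0.11 SD, false-positive rate about 7%.
- No true effect, 10% best and 10% worst removed in both arms: shift 0, rate 5%.
- True effect 0.72 SD (80% power with all 30 per group), common diagnosis rule removing 10% to 20% of controls: the estimate falls to 0.60 to 0.55 SD and power to 64% to 54%. Removal unrelated to outcome that left 27, 24 or 21 per arm would cost only power: 76%, 71% or 65%.

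**The case against.** The best defence is that a trial in CP should analyse children with CP, and that a diagnosis supported by lesions on imaging need not shift with two months of progress. Confirmation may come long after the outcome, and the outcome is a rate or acceleration of acquisition rather than a level. All this argues for a correlation well below 1, and it stands: the 0.26 and 0.27 SD figures are upper bounds within the model. It does not bring the correlation to zero, because the diagnosis may be clinical alone. Removing children found ineligible on baseline facts, judged blind to arm, could be defended, but the protocol sets no such limit.

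Section 2.3.2 also keeps the therapy-change rule from families so that it does not steer their decisions. That is a partial safeguard; it does not stop changes that follow progress, or decisions by unblinded staff.

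A reader might infer more than the text supports:

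- *That the comparison is biased.* With no true effect and the same mechanism in both arms it is not, and the diagnosis rule is permissive.
- *That eligibility for neuromotor disease contradicts removal for unconfirmed CP.* The rule requires a change of diagnosis as well as non-confirmation, so a stable neuromotor diagnosis does not trigger it.
- *That 2.3.2 both bans and allows concomitant therapy.* Its last sentence settles this: stable treatment is allowed and noted, while additions or withdrawals within the two months lead to exclusion. The drafting is awkward but not contradictory.
- *That infants treated late in a window ending December 2024 drop out as unconfirmed.* The rule refers to the appropriate age, there is an MRI route, and section 3 gives four years of data collection.
- *That the damage can never be repaired.* Therapy changes are recorded at the visit where outcomes are measured, so those children can be analysed. The difficulty is greater for at-risk children whose data may never enter the dataset.

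**Conclusion.** The concern holds as a risk built into the stated rules. Selection into the analysed set can depend on the child's course, and the between-group comparison is open to bias whose direction and size the documents do not determine. A common diagnosis rule mainly attenuates a real benefit: an assumed 0.5 SD becomes 0.26 SD at worst and 0.39 to 0.48 SD at correlations of 0.7 to 0.3, with 20% of controls removed. A spurious effect requires removal that differs by arm: 0.27 SD at worst and 0.19 to 0.08 SD at the same correlations, when the worst 15% of one arm go. Effect size, removal rates and correlations are all assumptions.

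One tension in the text also needs settling: section 2.3.1 admits at-risk children only after confirmation, then admits younger unconfirmed children on MRI risk. The second sentence can be read as an exception to the first, but the protocol does not say so, and two analysts could build different data sets.

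**What to change.** - Define eligibility from facts known at baseline: a confirmed diagnosis, or the MRI-based risk criterion already in section 2.3.1. Reconcile this with the sentence on retrospective inclusion.
- Keep every assigned child with consent in the main analysis, in the assigned group, whatever the later diagnosis or therapy change.
- Report diagnosis changes and therapy changes by arm, with reasons.
- Use the restricted set (CP confirmed by someone blind to arm, no therapy change) only as a sensitivity analysis.

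The cost is an amendment of wording; section 4 reports complete assessments for only four children so far. The downside is that some analysed children will prove not to have CP or will have had a therapy change, which dilutes the CP-only interpretation by an unknown amount. The fix also does not cure assignment by therapist availability (section 2.3), which is a separate threat to the comparison.

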### 2.5. Other Variables

Age.Diagnosis.Locomotion stage.Gross Motor Function Classification System.Previous and concomitant physiotherapy treatments.Occupational therapy.Hydrotherapy.Surgery.Botulinum toxin.Geographic background.

As we have mentioned previously, the participants in this research, within their care routine and according to the health protocols established in the Service, will be assigned to one of the following two study groups:Intervention group: patients under Vojta therapy intervention.Control group: patients under regular physiotherapy intervention.

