### 2.6. Sample Size Calculation and Statistical Analysis

Sample size calculation: The prevalence of cerebral palsy is 2.08 cases/1000 births. To obtain a good sample security, 30 subjects for each of the groups to be evaluated offer a confidence interval of 95% with a security of 10.

The initial GMFM and IMP score will be divided by the child’s months of age to calculate the rate of acquisition of their items so far. This calculation represents the mean distribution of the acquisition of these motor items. The acceleration values will be used to avoid errors in the assumption of how these items were acquired, since the tendency is to be exponential at these ages. The net values obtained in the valuation will not be considered, but the rate with which they have been obtained as a function of time will be. The rate of this development without intervention will be calculated at the time of the initial assessment, relative to the age of the patient. The proportion of the score necessary to obtain in the next two months to be able to accelerate that rate, instead of following the same previous trajectory, will be an unknown concept for all therapists and examiners.

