The rate values are calculated by dividing the total score by the time (days of age) required to achieve it, assuming that the neonatal GMFM would be zero. The acceleration factor is calculated by dividing the differences between final and initial rate (assumed to be zero at birth), by the age in days (elapsed time). The same rate and acceleration factors of acquisition are figured out between the initial assessment and after two months of the intervention. Only new points acquired during this period were considered to calculate the rate of development and acceleration values in the intervention period. Because the distribution of the item acquisition during the pre-intervention period is unknown, we performed a second rate calculation assuming that all the items were adquired during the last two months before the intervention (for children older than 2 months at initial assessment). This simulation of the maximal possible pre-intervention rate and acceleration will limit the possibility of being overcome by the post-treatment values and will avoid average values slowing down the last two preintervention months. Completing all the items in the previous two months is unlikely and would make it more difficult to obtain improvements after the intervention, especially for the older children. Even if these calculations do not benefit our results, they will ensure that the rate and acceleration post-intervention can be compared within same-lasting and following periods. We know that the GMFM item acquisition is not linear, and both calculations will help us to understand if the rate differences are due to natural acceleration or a significant therapeutic change. On the other hand, this will avoid comparing low average rate values due to longer pre-intervention periods and, therefore, random positive outcomes. Rate values within each GMFM dimension will then be considered and will help to clarify the results. 

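### The reason given for keeping children on background treatment contradicts the lifetime-average pre-treatment rate, so the effect of a recently started treatment shows largely as gain during study therapy

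*Protocol article*

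**What the plan says.** Section 2.3.2 gives two reasons for not excluding children on previous or concomitant treatment, such as drugs for spasticity, dystonia or epilepsy and other rehabilitation. The first is that "their effect would already be included within the rate of motor development before VT". The second is that "all the children were compared only to themselves". It adds "These will be noted and considered during the calculations", and that "the data exclusion will only occur if there are changes in them (both adding or withdrawal) during our 2 months of intervention". No condition applies to the period just before baseline.

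The rates are fixed elsewhere. Section 2.6: "The initial GMFM and IMP score will be divided by the child’s months of age to calculate the rate of acquisition". Discussion: "The rate values are calculated by dividing the total score by the time (days of age) required to achieve it". For the study period: "Only new points acquired during this period were considered to calculate the rate of development and acceleration values in the intervention period". The Discussion also defines a second pre-treatment rate for children older than 2 months at the initial assessment. It places all baseline items in the last two months and is offered as a deliberately unfavourable bound.

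Section 2.5 lists the recorded treatments, among them "Hydrotherapy.Surgery.Botulinum toxin". The Statistical Methods plan a repeated-measures ANOVA with time and treatment group as factors.

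**The concern.** The exclusion rule asks whether treatment changed during the two study months. The stated reason needs something else: that the treatment's effect is already in the comparison value. The two agree only if the treatment was in place for most of the child's life, because the main pre-treatment rate averages over all of it.

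A child who started a drug, began another therapy or had a procedure a few weeks before the initial assessment, with no change afterwards, satisfies the rule and stays in. The treatment acts through the whole intervention window but through only a small part of the period that forms the pre-treatment rate. In the within-child comparison its effect then looks like an effect of the study therapy. Section 3 relies on the short window to attribute change to that therapy and to control better for other therapy inputs.

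**Working it through.** The document gives no figure for this point, so there is none to reproduce. The check is algebra on the protocol's own definitions.

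**Inputs from the protocol.** Ages 0 to 36 months (section 2.3.1); main pre-rate = baseline score / age (section 2.6, Discussion); post-rate = new points over about 2 months (Discussion, section 3); second pre-rate = whole baseline score over 2 months (Discussion); 30 children per arm (section 2.6).

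**Assumptions.** Natural rate r; background treatment adds a constant e from time L before baseline and continues unchanged; age at baseline A; no effect of study therapy. The document gives no values for r, e or L. One month is taken as 30.4375 days for the leads stated in days.

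**Main rate**
- Pre = (rA + eL)/A = r + e·L/A
- Post = r + e
- Share of the effect in the pre-rate = L/A; share appearing as gain = 1 − L/A

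**Second rate**, in months, with L = 1
- Pre = (rA + e)/2, which contains 1/2 of e
- A false gain needs r + e > (rA + e)/2, that is e > (A − 2)·r

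| Age at baseline | L/A, 14-day lead | L/A, 1-month lead | L/A, 60-day lead | Shown as gain, main rate, 1-month lead | e/r needed for a false gain, second rate, 1-month lead |
|---|---|---|---|---|---|
| 3 months | 15% | 33% | 66% | 67% | 1 |
| 6 months | 8% | 17% | 33% | 83% | 4 |
| 12 months | 4% | 8% | 16% | 92% | 10 |
| 24 months | 2% | 4% | 8% | 96% | 22 |
| 36 months | 1% | 3% | 5% | 97% | 34 |

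Under the main rate, any positive e produces a false within-child gain. Under the second rate, a false gain is plausible only at the youngest ages. That protection comes from loading all earlier points onto two months, not from capturing the treatment's effect.

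**Between arms.** Let pV and pC be the proportions of recently treated children in the Vojta and conventional arms.
- Main rate: bias = e·(pV − pC)·(1 − L/A)
- Second rate, 1-month lead: bias = e·(pV − pC)·(1/2)

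The bias is zero if pV = pC. As an assumed illustration, 30% against 10% at 12 months of age with a 1-month lead gives 0.20 × 11/12 = 0.18e with the main rate and 0.20 × 1/2 = 0.10e with the second. At an assumed overall frequency of 20% and 30 per arm, chance alone gives an imbalance within 1.96 × √(2 × 0.2 × 0.8/30) = 0.20, or about ±20 percentage points. Allocation by therapist availability is not a random sequence, so even that range is not guaranteed.

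**The case against.** - **The second rate.** The protocol does not rest on the lifetime average alone. With a one-month lead the second rate holds half the effect, and beyond early infancy a false gain would need an effect several times the natural rate. This stands, and it limits the practical harm wherever both rates are reported. It does not rescue the reason in section 2.3.2, and the lifetime rate remains in use.
- **The control arm.** A reader might infer that the whole effect of recent background treatment is credited to Vojta therapy in the trial's result. The document does not support that: in the group-by-time test, equally common recent treatment cancels. Only an imbalance matters, and nothing in the text shows that one exists or that therapist slots are linked to recent treatment.
- **Restriction and recording.** It would also be wrong to say that background treatment is admitted without restriction. Additions and withdrawals during the two months lead to exclusion, treatments are recorded, and they are to be considered in the calculations. How they are considered may properly be left to an analysis plan. The incorrect justification, however, stands in this text, and an unspecified consideration does not correct it.
- **Age.** Saying that almost none of the effect is in the pre-rate would fit older children with short leads, but not young infants or longer leads, as the table shows.

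**Conclusion.** The point holds in limited form. The first reason in section 2.3.2 is inconsistent with the main rate in section 2.6 and the Discussion. For a one-month lead, 67% of the effect at 3 months of age and 97% at 36 months appears as within-child gain with no effect of study therapy. The second reason, self-comparison, does not help: that is the comparison in which the bias arises, and it is not the only one planned, since the Statistical Methods also compare groups.

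These shares assume an additive, constant effect that continues through the window; an effect that builds or fades would change them. How many children have recent treatment, and how large its effect is, cannot be learned from the document. No size can therefore be put on the bias between arms, and the 0.18e and 0.10e above are illustrations only. The correction is worth making because it is cheap and because the protocol uses this reasoning to justify attribution. It does not show that the arm comparison is invalid.

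**What to change.** 1. In section 2.3.2, replace the claim that the effect is already in the prior rate with a statement that the lifetime rate captures only long-standing treatment.
2. For the background treatments that sections 2.3.2 and 2.5 already record, collect the date of start, last change or procedure.
3. Prespecify a baseline item for any start, change or procedure in at least the 2 months before the initial assessment, defined identically in both arms. Keep time since start as well, because a 2-month cut-off misses earlier starts: at 24 months of age a treatment begun 3 months before baseline has only 3/24 = 12.5% of its effect in the lifetime rate.
4. Use the item as a covariate in the arm comparison. A covariate there does not correct the within-child change, so repeat both the within-child and the between-arm analyses without these children.

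The cost is one date field per treatment, one degree of freedom with 60 children planned, and one sensitivity analysis with a somewhat smaller sample. Eligibility and care do not change. The Discussion reports complete assessments for only four children, so dates can still be collected prospectively for nearly all of the planned sample.
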